#### 3.5.2. Secondary outcomes

Secondary outcomes include sleep timing metrics from the sleep tracker to understand if any changes in sleep timing lead to changes in sleep duration. The sleep timing metrics include sleep onset on weeknights and weekend nights (hours from 00:00), sleep offset on weeknights and weekend nights (hours from 00:00), and sleep midpoint on weeknights and weekend nights (hours from 00:00). “Social jetlag” will be calculated by subtracting the weekend night sleep midpoint from the weeknight sleep midpoint. Social jetlag provides an indication of the discrepancy between internal biological clocks and social requirements and has been linked to cardiometabolic risk (Cespedes Feliciano et al., 2019; Mathew et al., 2020). Sleep quality metrics will also be captured from the sleep tracker on weeknights and weekend nights: sleep efficiency (percentage of time spent asleep during overnight sleep periods), sleep onset latency (time to fall asleep), and wake after sleep onset (time awake during overnight sleep periods).

Secondary outcomes also include sleep disturbance and sleep impairment measured using the Patient-Reported Outcomes Measurement Information System (PROMIS) item bank for pediatric sleep (Forrest et al., 2018). This validated survey generates a sleep disturbance T-score based on items related to sleep onset, sleep continuity and sleep quality in the past week. The survey also generates a sleep-related impairment T-score based on items related to daytime sleepiness, cognition, affect and behavior, and daytime activities in the past week. Higher T-scores indicates poorer sleep quality (Forrest et al., 2018). Participants will complete this survey at baseline and at the end of each month during the intervention and follow-up phases.

Secondary outcomes will also be considered with respect to body composition and size. These include visceral body adipose tissue area (cm^2^), waist circumferences (cm), and BMI (kg/m^2^).

### 3.6. Power calculation

#### 3.6.1. Aim 1

The primary outcome for Aim 1 is nighttime sleep duration (hours per night) on weeknights (measured daily by the sleep tracker). The “MOST” R package (FactorialPowerPlan) was used to determine the sample size needed to detect a 30 min per night difference in nighttime sleep duration on weeknights (alpha = 0.05; power = 0.8; pretest-posttest correlation of sleep duration = 0.7; and a standard deviation sleep duration = 0.7 h per night). The effect size and parameters were derived from our prior studies. The calculation accounted for detection of main effects plus all possible interactions. The power calculation revealed that a minimum sample size of 41 was needed for Aim 1.

#### 3.6.2. Aim 2

The primary outcome for Aim 2 is fat mass index (kg/m^2^) (measured at baseline, 6-months, and 12-months by DXA). The “MOST” R package (FactorialPowerPlan) was used to determine the sample size needed to detect a 0.25 kg/m^2^ reduction in fat mass index at 6-months and 12-months (alpha = 0.05; power = 0.8; pretest-posttest correlation of fat mass index = 0.9; and a standard deviation for fat mass index = 0.9). The effect size and parameters were derived from our prior studies. The calculation accounted for detection of main effects plus all possible interactions. The power calculation revealed that a minimum sample size of 282 was needed for Aim 2.

#### 3.6.3. Aim 3

The primary outcome for Aim 3 is nighttime sleep duration (hours per night) on weeknights (measured daily by the sleep tracker). It has been observed that male children sleep on average 12 min per night less than female children, and that African American/Black children sleep on average 33 min per night less than non-Latinx White children (Guglielmo et al., 2018; Billings et al., 2021; Min et al., 2021). We will determine if the effectiveness of the optimal component settings for sleep promotion differ by ≥20 min across sociodemographic factors. This calculation revealed that 286 participants are needed to detect a ≥20 min per night difference in the effectiveness of the optimal component settings for sleep duration by higher and lower sociodemographic levels. The calculation was completed in Stata (version 14.2) using the “power repeated” command to compute the sample size. The parameters used for the calculation were: alpha = 0.05, power = 0.8, number of repeated measures = 52, number of groups = 2, error variance = 1.1, and correlation = 0.7.

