## 3. Methods

### 3.1. Study design

A 2^4^-factorial design (i.e., 16 study conditions) will be used to address the study objectives (Table 1). A two-week run-in phase will be used to measure baseline sleep duration, a 6-month intervention phase will be used to measure changes in sleep duration from baseline, and a ≈5.5-month follow-up phase will be used to measure if there are lasting changes in sleep duration from baseline. Clinical measurements (e.g., DXA, 24 h dietary recalls) will be obtained at baseline, 6-months, and 12-months at the Children's Hospital of Philadelphia (CHOP).

**Table 1 T1:** The 2^4^ factorial study design.

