#### 3.6.4. Final sample size

We elected to randomize 325 children. Accounting for an attrition rate of 10%, the study has a sample size that is powered to detect clinically relevant differences in the primary outcomes under each aim.

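### The Aim 2 minimum sample size of 282 cannot be reproduced from its printed inputs; the method that returns Aim 1's 41 exactly gives 84

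*Protocol article*

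**What the plan says.** Sections 3.6.1 and 3.6.2 of the protocol article describe two calculations made in the same way. Both name the same program ("The “MOST” R package (FactorialPowerPlan) was used to determine the sample size needed"), both use alpha 0.05 and power 0.8, both supply a pretest-posttest correlation, and both carry the statement "The calculation accounted for detection of main effects plus all possible interactions". The design is the same for both: "A 2^4^-factorial design (i.e., 16 study conditions) will be used to address the study objectives".

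- **Aim 1 (weeknight sleep duration):** effect 30 min, SD 0.7 h, correlation 0.7. Result: "The power calculation revealed that a minimum sample size of 41 was needed for Aim 1".
- **Aim 2 (fat mass index):** the sample size is the one "needed to detect a 0.25 kg/m^2^ reduction in fat mass index at 6-months and 12-months", with "pretest-posttest correlation of fat mass index = 0.9; and a standard deviation for fat mass index = 0.9". Result: "The power calculation revealed that a minimum sample size of 282 was needed for Aim 2".

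Section 3.6.3 gives 286 for Aim 3, by a different program. Section 3.6.4 sets 325 to be randomized with 10% attrition and concludes that "the study has a sample size that is powered to detect clinically relevant differences in the primary outcomes under each aim".

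**The concern.** The two calculations differ only in effect, SD and correlation, so one method should return both results. The printed inputs make Aim 2 the harder target, but not by the factor of nearly seven that separates 41 from 282. The high correlation of 0.9 removes most of the outcome variance, and this offsets much of the smaller standardized effect (0.25/0.9 = 0.28, against 0.5/0.7 = 0.71 for Aim 1).

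What is at stake is how the fat mass index result can be read. The claim in section 3.6.4 that the trial is powered for clinically relevant differences depends on knowing which difference that is. As printed, the detectable effect could be about 0.13 or about 0.25 kg/m². The same inputs might also be carried into planning the evaluation-phase trial that sections 4 and 5 anticipate.

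**Working it through.** **Method.** In a balanced 2^4 design with effect coding, the test of one coefficient in the full model (16 coefficients) is an F test on 1 and N − 16 degrees of freedom, with noncentrality

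λ = N·δ² / (4·v).

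Here δ is the difference between the two levels of a factor and v is the residual variance:

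- pretest as repeated measure (change score): v = 2·SD²·(1 − r)
- pretest as covariate: v = SD²·(1 − r²)
- no pretest: v = SD²

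N is the smallest total with power of at least 0.80. The article does not state sidedness or how the pretest enters. The F test at alpha 0.05 (equivalent to a two-sided test) is assumed, and the alternatives are tried below.

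**Step 1: reproduce Aim 1.** δ = 0.5 h, SD = 0.7, r = 0.7.

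- v = 2 × 0.49 × 0.3 = 0.294
- At N = 41: λ = 41 × 0.25 / (4 × 0.294) = 8.72, power 0.81
- At N = 40: power 0.799, just short

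The result is 41, exactly as printed. The covariate form gives 35 and no pretest gives 65, so the repeated-measure form is the one that matches.

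**Step 2: the same method for Aim 2.** δ = 0.25, SD = 0.9, r = 0.9.

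- v = 2 × 0.81 × 0.1 = 0.162
- At N = 84: λ = 84 × 0.0625 / (4 × 0.162) = 8.10, power 0.801
- At N = 83: power 0.796

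The result is 84, against 282 printed (282/84 = 3.4). At N = 282 the printed inputs give λ = 27.2 and power 0.999, not 0.8.

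**Step 3: settings the article does not state.** All use the printed 0.25 / 0.9 / 0.9. Rows use the repeated-measure form, 16 coefficients, alpha 0.05 and power 0.80 unless noted.

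| Variant | N |
|---|---|
| Pretest as covariate | 80 |
| No pretest | 409 |
| 2 to 32 coefficients | 84–85 |
| Alpha 0.10 | 66 |
| Bonferroni over 2, 3, 4, 15 tests | 102, 112, 120, 153 |
| Power 0.90, 0.95, 0.99 | 112, 137, 193 |
| Effect entered at half size | 328 (covariate 312) |

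None gives 282. Attrition does not explain the gap, because section 3.6.4 applies it afterwards.

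**Step 4: what 282 would require.** Changing one input at a time, in the repeated-measure form:

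- an effect of about 0.135 kg/m² instead of 0.25, or
- an SD of about 1.67 instead of 0.9, or
- a correlation of about 0.66 instead of 0.9.

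A standardized effect of 0.15 with r = 0.9 returns exactly 282 (0.135/0.9 = 0.15).

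**Step 5: consequence at the planned size.** 325 × 0.9 = 292.5, so about 292 completers.

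- Printed inputs right: power for 0.25 kg/m² exceeds 0.999, and the main effect detectable with 80% power is about 0.13 kg/m².
- 282 and the 0.25 effect right, with the SD (1.67) or the correlation (0.66) misprinted: the detectable effect is about 0.25 kg/m².
- 282 right and the effect misprinted (0.135): the detectable effect is again about 0.13 kg/m², but 0.25 is not what the trial was sized for.

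**The case against.** Four points can be made for the plan.

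1. **Enrolment is safe either way.** If 84 is right, 292 completers far exceed it; if 282 is right, they still cover it. Aim 3's 286 is the larger stated requirement, and 286/0.9 = 318 supports a figure near 325 without Aim 2. This stands, and it limits the point to a sample-size statement that its own inputs do not support.

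2. **The article does not print the program call.** An unreported setting could have been used, and the target is worded for both 6 and 12 months while the check uses one post-test. This stands in part. Allowing for two tests brings the figure only to 102, but a setting that was not tried cannot be excluded. The conclusion is therefore that a figure is wrong or an input is missing.

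3. **282 may have been computed correctly from other inputs.** The exact match at a standardized effect of 0.15 points to a misreported effect or SD. That is a useful clue, but the article does not confirm it.

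4. **A reader might infer that interactions are underpowered, so that the statement about detecting all interactions overstates the design.** The documents do not support this. Section 3.7.1 plans effect coding, and in a balanced 2^4 design a main-effect and an interaction coefficient of equal size have equal power. A low figure appears only if the interaction is redefined as a difference between simple effects and 282 is taken as right.

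**Conclusion.** The point holds: 282 does not follow from the printed Aim 2 inputs. The method that matches the article's Aim 1 figure exactly gives 84, a 3.4-fold gap, and none of the variants tried closes it. Either the effect, SD, correlation or N is misprinted, or an input was left out of the text. The exact match at a standardized effect of 0.15 suggests that the effect or SD is the misprint, but does not prove it.

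This rests on a balanced 2^4 allocation, an F test at alpha 0.05 and the repeated-measure form, which is inferred from its match to 41.

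Two stronger readings are not supported. The trial is not shown to be too small for Aim 2, since 292 completers cover the main effect under either reading. Nor do these figures say which fat mass index effects a null result would exclude; that depends on the confidence interval obtained, not on planned power.

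**What to change.** Rerun the Aim 2 calculation from the original program call. Then correct whichever of the effect, SD, correlation or 282 is wrong, or report the input that was used but not stated. Give the pretest mode and sidedness alongside, so that both 41 and the Aim 2 figure can be reproduced. Restate in section 3.6.4 the fat mass index main effect detectable with 80% power at about 292 completers.

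Leave the 325 unchanged. The cost is one recalculation and a corrected paragraph, with no effect on enrolment, conduct or the analysis model.

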### 3.7. Statistical plan

Under the intent to treat principle, we will use all available data and participants under the assumption of missingness at random. No participants will be excluded from the analysis except for the unlikely case of no outcome measurements for a participant. Final models will be adjusted for covariate dependent missingness due to dropout. We will examine sensitivity to the assumptions about the missing data mechanism.

#### 3.7.1. Aim 1

Mixed-effects linear regression models will be used to determine if the intervention components are associated with changes in weeknight sleep duration from baseline. The fixed model components will include indicators for each factor (with effect coding used to identify each component level), time in weeks, and all possible interactions between time and factors. The full model will be reduced to a more parsimonious model by selecting the main effects and interactions achieving a Type I error rate of alpha = 0.05.

#### 3.7.2. Aim 2

Mixed-effects linear regression models will be used to measures changes in fat mass index using the most parsimonious model from Aim 1 (i.e., optimal component settings for sleep promotion).

#### 3.7.3. Aim 3

The most parsimonious model from Aim 1 (i.e., optimal component settings for sleep promotion), will be expanded to determine if effectiveness differs by sociodemographic factors. The fixed model components will include indicators for each component (effect coding to represent the levels of each factor), time in weeks, the sociodemographic factor of interest, interactions between time, component(s), and sociodemographic factor. The sociodemographic factors that will be modeled include sex, race/ethnicity, and neighborhood context (poverty, sound, canopy cover, housing and population density, and street connectivity).

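### The Aim 3 figure of 286 for 80% power comes from a two-group calculation, but the planned test is a component-by-sociodemographic interaction, so the stated power is unsupported

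*Protocol article*

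**What the plan says.** Section 3.6.3 of the protocol article sets the Aim 3 target: "We will determine if the effectiveness of the optimal component settings for sleep promotion differ by ≥20 min across sociodemographic factors". The sample size sentence reads "This calculation revealed that 286 participants are needed to detect a ≥20 min per night difference in the effectiveness of the optimal component settings", and it continues "for sleep duration by higher and lower sociodemographic levels". On method it says "The calculation was completed in Stata (version 14.2) using the “power repeated” command to compute the sample size". The inputs are listed in full: "The parameters used for the calculation were: alpha = 0.05, power = 0.8", then "number of repeated measures = 52, number of groups = 2, error variance = 1.1, and correlation = 0.7".

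Section 3.7.3 gives the analysis. The reduced Aim 1 model, which concerns change in weeknight sleep from baseline, is extended with "interactions between time, component(s), and sociodemographic factor". Table 1 and section 3.1 define a 2^4 factorial, so each level of each component is held by half the children.

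Section 3.6.1 sizes Aim 1 on the same outcome, with a correlation of 0.7 and "a standard deviation sleep duration = 0.7 h per night". Section 3.6.4 randomizes 325, allows 10% attrition, and says that the trial is powered under every aim.

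**The concern.** The effectiveness of a component is a contrast between its two levels. A difference in effectiveness between two sociodemographic levels is a difference between two such contrasts and needs four cells. The calculation has two groups, the higher and lower sociodemographic levels. No input stands for component level, the share of children exposed, or baseline adjustment. The calculation and the planned test therefore address different contrasts.

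This matters because the Aim 3 hypothesis in section 1.9 is that the optimal settings work equally well across groups. A non-significant interaction would be read as support for equity, and that reading leans on the claim of 80% power to see a 20-minute difference.

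**Working it through.** **Inputs.** From section 3.6.3: alpha 0.05, power 0.80, 52 measures, error variance 1.1 h², correlation 0.7, difference 20 min = 0.333 h. From section 3.6.1: SD 0.7 h, so variance 0.7² = 0.49 h². From section 3.6.4: 325 × 0.9 = 292.5, taken as 292 completers. Assumed, because not stated: two-sided test; constant correlation at all lags; one baseline week and 51 later weeks for the adjusted versions; one component contrasted at its two levels. The sociodemographic split is shown at 50:50 and at an assumed 20:80.

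**Step 1: the plan's own figure.** The variance of a child's 52-measure mean is 1.1 × (1 + 51 × 0.7)/52 = 0.776 h². For two equal groups, N = 4 × 0.776 × (1.960 + 0.842)²/0.333² = 220 by the normal approximation, or 222 by the exact F test. The stated 286 is not reproduced. At 286 this two-group test has about 89% power.

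Other readings miss 286 too: 370 for a group-by-time test with one baseline measure and then a constant gap, and 293 for a 25:75 split. Values near 286 appear only when an input is changed, for example correlation 0.9 (284). None of these adds a component dimension.

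**Step 2: the planned contrast.** With share p in one sociodemographic level and half the sample at each component level, the difference in differences has SE² = V/(N × 0.25 × p(1−p)). At p = 0.5 this is 16V/N, against 4V/N for two equal groups: four times the variance.

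**Step 3: the variance V that applies.** Let σ² be 1.1 or 0.49.
- Unadjusted 52-week mean: σ²(1 + 51 × 0.7)/52 = 0.776 or 0.346.
- Change from baseline: σ² × 0.3 × (1 + 1/51) = 0.336 or 0.150.
- Baseline as covariate: σ²[(1 + 50 × 0.7)/51 − 0.7²] = 0.237 or 0.106.

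Example: with V = 0.776, N = 292 and p = 0.5, SE = √(16 × 0.776/292) = 0.206 h = 12.4 min. The z-value is 20/12.4 = 1.62 and power is about 37%.

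**Step 4: power for a 20-minute interaction at 292.**

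| Variance | Split | Unadjusted | Change score | Baseline as covariate |
|---|---|---|---|---|
| 1.1 | 50:50 | 37% | 69% | 83% |
| 1.1 | 20:80 | 25% | 50% | 65% |
| 0.49 | 50:50 | 68% | 96% | 99% |
| 0.49 | 20:80 | 49% | 84% | 94% |

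**Step 5: detectable difference.** At 292, an even split and 80% power, the detectable difference is 2.802 × SE. With variance 1.1 this is about 35, 23 and 19 min for the three versions. With 0.49 it is about 23, 15 and 13 min.

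**The case against.** The strongest reply is that the low figures do not model the planned analysis. Section 3.7.1 works with change from baseline and Aim 3 extends that model, so the unadjusted column shows only what the printed inputs imply. With baseline as covariate and an even split, power exceeds 80% even at variance 1.1. At Aim 1's variance, both baseline-adjusted versions exceed 80% even at 20:80. This stands. A reader might infer from the fourfold variance that Aim 3 is underpowered, but the documents do not support that as a flat statement.

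A reader might also infer that 286 was miscalculated. That is not shown: the article does not say whether the between-group or the group-by-time effect was tested, or what allocation was used. As a plain comparison of two equal groups, 286 would be more than enough.

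The two variances may not be like for like, since one is an SD in a pretest-posttest calculation and the other an error variance over 52 measures. This is possible, but the article does not explain it.

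Finally, 325 barely depends on Aim 3: Aim 2 needs 282, about 313 after 10% attrition, against about 318 for Aim 3. This limits the practical consequence. None of these replies supplies the missing component dimension.

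**Conclusion.** The point holds as a mismatch between calculation and test. The 80% belongs to a comparison of two sociodemographic groups, not to the interaction that Aim 3 will test, so it should not stand as written. Across the scenarios above, power at 292 runs from 25% to 99%. For the baseline-adjusted versions, which are closer to the plan, it runs from 50% to 99%. The position within that range depends on the variance, the form of baseline adjustment and the group shares, none of which the calculation settles. All figures assume constant correlation of 0.7, a two-sided test and a single component contrast. This should be fixed before Aim 3 is interpreted, but it does not threaten the conduct of the trial.

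**What to change.** Recompute Aim 3 as the component-by-group interaction in the planned change-from-baseline model. Use one justified variance for Aims 1 and 3, or explain why they differ, and use expected rather than equal group shares. State which effect the software call tests. Replace the 286/80% statement with the achieved power, or the minimum detectable difference in effectiveness, at 292 completers, as a range if the variance remains uncertain. Do not raise enrolment on this account. State that a null interaction will not be read as evidence of equity on the strength of the present 80% figure. The cost is one recalculation and a reworded paragraph; the restated power may be lower or higher than 80%.

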#### 3.6.4. Final sample size

We elected to randomize 325 children. Accounting for an attrition rate of 10%, the study has a sample size that is powered to detect clinically relevant differences in the primary outcomes under each aim.

### 3.7. Statistical plan

Under the intent to treat principle, we will use all available data and participants under the assumption of missingness at random. No participants will be excluded from the analysis except for the unlikely case of no outcome measurements for a participant. Final models will be adjusted for covariate dependent missingness due to dropout. We will examine sensitivity to the assumptions about the missing data mechanism.

#### 3.7.1. Aim 1

Mixed-effects linear regression models will be used to determine if the intervention components are associated with changes in weeknight sleep duration from baseline. The fixed model components will include indicators for each factor (with effect coding used to identify each component level), time in weeks, and all possible interactions between time and factors. The full model will be reduced to a more parsimonious model by selecting the main effects and interactions achieving a Type I error rate of alpha = 0.05.

#### 3.7.2. Aim 2

Mixed-effects linear regression models will be used to measures changes in fat mass index using the most parsimonious model from Aim 1 (i.e., optimal component settings for sleep promotion).

#### 3.7.3. Aim 3

The most parsimonious model from Aim 1 (i.e., optimal component settings for sleep promotion), will be expanded to determine if effectiveness differs by sociodemographic factors. The fixed model components will include indicators for each component (effect coding to represent the levels of each factor), time in weeks, the sociodemographic factor of interest, interactions between time, component(s), and sociodemographic factor. The sociodemographic factors that will be modeled include sex, race/ethnicity, and neighborhood context (poverty, sound, canopy cover, housing and population density, and street connectivity).

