#### 3.3.6. Follow-up phase

Participants will be asked to continue to wear the sleep tracker device to capture sleep patterns with all intervention components inactivated for ≈5.5 months follow-up phase. The purpose is to determine if any changes in sleep duration persist over time.

Dietary intake will be captured during the final month of the follow-up phase via three 24-h dietary recalls. Sleep diaries will be completed by all participants for 1 week in months 8, 10, and 12. Participants will also complete monthly surveys at the end of each month to continue to assess self-reported sleep data (PROMIS surveys) and mediators.

#### 3.3.7. Visit 3

The caregiver and child will complete questionnaires. In addition, the child will complete anthropometric measures and a DXA scan. These measures will all be the same as those completed at Visits 1 and 2. This visit will be scheduled to occur 12-months after randomization, with a 4-week window in anticipation of scheduling issues.

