##### 3.5.1.1. Optimization objective

The optimal component settings will have to meet the following criteria: increase average baseline sleep duration on weeknights by ≥30 min for ≥75% of intervention weeks and for ≥50% of follow-up weeks. A 30-min increase in sleep duration has been shown to be feasible in our prior research (Mitchell et al., 2021) and has been shown to improve alertness and emotional regulation (Gruber et al., 2012) and to lower weight gain (Hart et al., 2022).

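### The Aim 1 model lists time only as weeks, with no term for phase; if week is a linear trend over the year, it blurs the intervention and follow-up effects that the optimization rule needs kept apart

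*Protocol article*

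**What the plan says.** For the first aim, section 3.7.1 names the method: "Mixed-effects linear regression models will be used to determine if the intervention components are associated with changes in weeknight sleep duration from baseline". Its fixed part holds effect-coded indicators for each factor, "time in weeks, and all possible interactions between time and factors". A reduction step at the 0.05 level follows: "The full model will be reduced to a more parsimonious model by selecting the main effects and interactions achieving a Type I error rate of" that size. Section 3.7.3 (Aim 3) expands the reduced model and again enters time in weeks. Section 3.7.2 (Aim 2) applies the reduced model to fat mass index. Both sections treat the reduced model as the optimal component settings.

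The design has phases. Section 3.1: "a 6-month intervention phase will be used to measure changes in sleep duration from baseline". Section 3.3.6: the tracker is then worn "with all intervention components inactivated for ≈5.5 months follow-up phase", and the section gives its reason: "The purpose is to determine if any changes in sleep duration persist over time". Section 3.5.1.1 sets the optimization rule by phase: baseline weeknight sleep must rise "by ≥30 min for ≥75% of intervention weeks and for ≥50% of follow-up weeks".

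**The concern.** The trial asks two questions that differ by phase: what a component does while it is active, and what remains once it is off. The listed terms contain nothing that changes at switch-off. A linear term in week gives each component one intercept and one slope for the whole year. An effect that starts at activation and ends at about week 26 must then be spread along a line, which understates the intervention phase, overstates follow-up and creates an apparent decline while the component is still on. The same model supplies the settings carried into Aims 2 and 3, so the form of the time term matters beyond Aim 1.

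**Working it through.** **The plan's own figure.** Section 3.6.1 gives a difference of 0.5 h, SD 0.7 h, pre-post correlation 0.7, alpha 0.05 (taken as two-sided), power 0.8 and all interactions in the model (16 cell parameters).
- Change-score variance = 2 × 0.7² × (1 − 0.7) = 0.294.
- Noncentrality = N × 0.5² / (4 × 0.294), with N − 16 error degrees of freedom.
- The smallest N with power of at least 0.80 is 41, as stated. The figure is sized for a pre-post difference in level, not a weekly slope, so the concern does not touch it.

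**Assumptions for the check (not given in the article).**
- One baseline week (t = 0), since section 3.3.2 takes baseline from the second run-in week.
- 26 intervention weeks (t = 1 to 26) for 6 months, and 24 follow-up weeks (t = 27 to 50) for about 5.5 months.
- Complete, balanced data. The mixed-model fixed effects then equal the least-squares line through the component effect by week.
- The effect profiles are illustrative.

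**Effect of 30 min on, 0 off.**
- Mean of t = 25; sum of (t − 25)² = 11,050.
- Cross-product = 30 × (351 − 26 × 25) = 30 × (−299) = −8,970.
- Slope = −8,970 / 11,050 = −0.812 min per week.
- Mean effect = 26 × 30 / 51 = 15.29; intercept = 15.29 + 0.812 × 25 = 35.6 min at week 0, where the true effect is 0.
- Fitted intervention mean (mean t = 13.5) = 24.6 min, against 30.
- Fitted follow-up mean (mean t = 38.5) = 4.3 min, against 0.
- Fitted effect at week 26 = 14.5 min, against 30.

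Leaving out the baseline week, as a change-from-baseline outcome would, gives 26.4 and 3.9 min, with 15.2 min at week 26. In 500 simulated trials of 292 children (325 less 10%), the linear-week model averaged 24.7 and 4.5 min; a phase or categorical-week contrast averaged 30.1 and 0.1 min. That simulation assumed a between-child SD of 35 min and a weekly within-child SD of 23 min, which set the noise and not the bias.

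**Profiles that truly meet both limbs of the rule (at least 75% and at least 50% of weeks).** The rule is scored here from the fitted line.

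| True profile | True weeks ≥30 min (intervention / follow-up) | Fitted, baseline week in | Fitted, baseline week out |
|---|---|---|---|
| 36 min to week 39, then 0 | 100% / 54% | 81% / 0% | 85% / 0% |
| 8-week ramp to 36, then linear fade to 25 by week 50 | 77% / 54% | 12% / 100% | 62% / 100% |
| 36 on, then 30 sustained | 100% / 100% | 100% / 100% | 100% / 67% |
| 36 throughout | 100% / 100% | 100% / 100% | 100% / 100% |

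In the first row the fitted line is 26.3 min at week 27 and falls from there, so no follow-up week reaches 30. In the second it starts at 27.2 and rises 0.117 per week, so only weeks 24 to 26 (3 of 26) reach 30. Both rows fail wrongly; the last two pass correctly.

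**Slow fade.** With 36 on and a linear fade to 0 by week 50, the true phase means are 36.0 and 17.2 min. The fitted means are 33.7 and 18.0 (35.7 and 17.5 without baseline), a small distortion.

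**Size of the models.** Linear week: 2 × 16 = 32 fixed effects. Three-level phase: 3 × 16 = 48. Categorical week: 51 × 16 = 816.

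**The case against.** The strongest reply is that the straight line is the reader's assumption. The article says time in weeks, not linear time; linear regression does not make time linear; and the text speaks of models in the plural. Categorical week, or separate models by phase, would recover both phase effects without bias, and neither is excluded. This stands, so a reader who infers that the stated analysis cannot recover the phase effects goes further than the text. Linear week is still the more natural reading: indicators are mentioned only for the factors, and 816 fixed effects reduced by significance would hardly be workable. A single model over the year is likewise inferred, from the use of all available data, the 260 weeknights in section 3.5.1 and the 52 repeated measures in section 3.6.3.

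A second reply is that a condensed article may leave the coding of time to the full plan. That tempers the severity. But section 3.7.1 does list the fixed effects, the interactions and the selection rule, and that list does not match a rule defined by phase.

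Three further points limit the claim.
- The 30/0 profile reaches 30 min in no follow-up week, so it fails the rule under any model. It shows bias in the effects, not a wrong decision, and counting its weeks at exactly the threshold would be a knife-edge.
- The rule concerns the rise from baseline under a setting, not a component contrast, and nothing says that it will be scored from fitted values.
- A reader might infer that effective components would be dropped at the 0.05 step. The 30/0 fit still has a large intercept and a non-zero slope, so the component would tend to be kept; the error lies in the shape over time.

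Nor does the categorical reading imply dozens of chance findings. About 37 of 750 factor-by-week terms (750 × 0.05 = 37.5) assumes that week dummies are tested one at a time. Tested jointly, 15 factorial effects by week give 15 × 0.05 = 0.75.

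**Conclusion.** The concern holds in conditional form. As listed, the Aim 1 and Aim 3 models have no phase or change-point term, while the components and the decision rule both change at switch-off. If week enters linearly over the whole year, an abrupt on/off effect of 30 and 0 min is reported as about 25 and 4 min with a spurious decline. If the optimization rule is then read from that fit, some settings that meet both limbs are classed as failing. Effects that persist or fade slowly are distorted little. The result rests on linear week, one model for the year, a 26 + 24 week split, complete data and illustrative profiles. It is worth settling before analysis, because the primary result and the settings carried into Aims 2 and 3 depend on it.

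**What to change.** In section 3.7.1, replace linear time in weeks with a three-level phase term (baseline, intervention, follow-up), with optional slopes within phase and a knot at switch-off. Name factor-by-intervention-phase, relative to baseline, as the primary Aim 1 contrast, and factor-by-follow-up-phase as the persistence contrast. Use the same form in section 3.7.3, and say whether the section 3.5.1.1 rule is scored from model estimates or from observed weekly means. If the full plan already uses categorical week or separate models by phase, stating that together with the phase contrasts would answer the point.

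The cost is plan wording and about 48 fixed effects instead of 32, or more with within-phase slopes. No new data are needed, and the sample size stands.
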